## Abstract

**Background:**

The primary objective is to determine the proportion of men with suspected prostate cancer (PCA) in whom the management plans are changed by additive gallium-68 prostate-specific membrane antigen positron emission tomography/computed tomography (PSMA-PET/CT) guided prostate biopsy (PET-TB) in combination with standard of care (SOC) using systematic (SB) and multiparametric magnetic resonance imaging-guided biopsy (MR-TB) compared with SOC alone. The major secondary objectives are to determine the additive value of the combined approach of SB + MR-TB + PET-TB (PET/MR-TB) for detecting clinically significant PCA (csPCA) compared to SOC; to determine sensitivity, specificity, positive and negative predictive value and diagnostic accuracy of imaging techniques, respective imaging classification systems, and each biopsy method; and to compare preoperatively defined tumor burden and biomarker expression and pathological tumor extent in prostate specimens.

**Methods:**

The DEPROMP study is a prospective, open-label, interventional investigator-initiated trial. Risk stratification and management plans after PET/MR-TB are conducted randomized and blinded by different evaluation teams of experienced urologists based on histopathological analysis and imaging information: one including all results of the PET/MR-TB and one excluding the additional information gained by PSMA-PET/CT guided biopsy. The power calculation was centered on pilot data, and we will recruit up to 230 biopsy-naïve men who will undergo PET/MR-TB for suspected PCA. Conduct and reporting of MRI and PSMA-PET/CT will be performed in a blinded fashion.

**Discussion:**

The DEPROMP Trial will be the first to evaluate the clinically relevant effects of the use of PSMA-PET/CT in patients with suspected PCA compared to current SOC. The study will provide prospective data to determine the diagnostic yields of additional PET-TB in men with suspected PCA and the impact on treatment plans in terms of intra- and intermodal changes. The results will allow a comparative analysis of risk stratification by each biopsy method, including a performance analysis of the corresponding rating systems. This will reveal potential intermethod and pre- and postoperative discordances of tumor stage and grading, providing the opportunity to critically assess the need for multiple biopsies.

**Trial registration:**

German Clinical Study Register DRKS 00024134. Registered on 26 January 2021.

**Supplementary Information:**

The online version contains supplementary material available at 10.1186/s13063-023-07197-0.

## Administrative information

Note: The numbers in curly brackets in this protocol refer to the SPIRIT checklist item numbers. The order of the items has been modified to group similar items (see http://www.equator-network.org/reporting-guidelines/spirit-2013-statement-defining-standard-protocol-items-for-clinical-trials/).

## Introduction

### Background and rationale {6a}

Prostate cancer (PCA) is biologically characterized by strong inter- and intratumoral heterogeneity, making it challenging to differentiate indolent cancer (International Society of Urological Pathology (ISUP) grade 1 PCA, nsPCA) from potentially lethal, clinically significant carcinomas (≥ ISUP grade 2 PCA, csPCA). PCA and its treatment affect patients’ quality of life in several areas [1, 2].

Increasing individualized therapy strategies drive the importance of reliable risk stratification during initial staging to adjust clinical management plans. Multiparametric magnetic resonance imaging of the prostate (MRI) has improved the detection of csPCA with a sensitivity of 88% and beneficially reduced the detection of nsPCA [3]. Guidelines recommend MRI before prostate biopsy, and its use has steadily increased worldwide [4]. Nevertheless, the detection accuracy of the MRI depends on cancer differentiation and is limited by a rather low PPV of 34–65% [3, 5]. Hence, the debate persists about whether MRI-targeted biopsy (MR-TB) should be used in place of systematic biopsy (SB) or in conjunction with it. Despite the higher detection of csPCA by the combined approach, a sampling error in one-third of patients is still to be expected [6]. Since morbidity-associated, cost-intensive diagnostic, and therapeutic measures are based upon biopsy results, there is a need to optimize the biopsy pathway.

Additional imaging and/or biomarkers could improve risk stratification. The prostate-specific membrane antigen (PSMA) seems to be both a promising biomarker and a key element for improved imaging for PCA detection. Its expression is associated with high-grade cancer, increased tumor progression, and the risk of early biochemical recurrence [7, 8]. Today, gallium-68 PSMA positron emission tomography/computed tomography (PSMA-PET/CT) is primarily used in cases of biochemical recurrence and for primary staging of high-risk patients and has limited availability [9, 10]. However, based on its high diagnostic accuracy, clinical utility, and recent approval by the US Food and Drug Administration for the detection of PCA, PSMA-PET/CT is expected to contribute significantly to the diagnostic process of primary PCA in the future.

Several recent series have already demonstrated improved intraprostatic diagnostic accuracy for PCA using PSMA-PET/CT compared to MRI [11–13] and the utility of PSMA-PET/CT-guided fusion biopsy (PET-TB) to optimize PCA detection [14, 15]. The combined approach of PSMA-PET/CT and MRI results in improved csPCA detection with enhanced NPV of 91% in biopsy-naïve patients [16] and an optimized description of local tumor extension, both crucial for the management planning [17]. Moreover, a significant impact on treatment strategies by PSMA-PET/CT was shown for PCA-proven men, resulting in intra- and inter-modal adjustments of management in up to 75% of men [18] and an optimized discrimination between unifocal, multifocal, and oligometastatic disease, decisive for individualized targeted and multimodal PCA-management [19, 20]. However, the gain in information through optimized initial staging raises previously unanswered questions: Which findings result in treatment changes and which patients benefit from altered therapy management?

Valid study results on these questions are currently not available. The DEtection rate of clinically significant PROstate cancer by mpMRI and PSMA-PET/CT fusion biopsy (DEPROMP) trial aims to determine the benefit of additive PET-TB and its impact on the diagnostic and therapeutic algorithm of PCA patients. Hereby, the combined approach of SB, MR-TB, and PET-TB (PET/MR-TB) has the potential to increase the detection of csCPA, improve the assessment of tumor extent and stage, and subsequently ameliorate the management of PCA patients significantly.

### Objectives {7}

The DEPROMP Trial aims to determine the clinically relevant effects of the additive use of PSMA-PET/CT in biopsy-naïve patients with suspected PCA compared to current SOC. In particular, its influence on medical treatment planning and on the detection of csPCA is investigated. A detailed explanation of the study objectives is presented in Table 1.

**Table 1 Tab1:** Study objectives

**Primary objective**
➢ To determine the proportion of patients in whom management plans are changed by additional PET-TB compared to the SOC using SB and MR-TB
**Secondary study objectives**
➢ To determine the additive value of PET/MR-TB for detecting csPCA in men undergoing initial biopsy for suspected PCA compared to SOC
➢ To determine sensitivity, specificity, PPV, NPV, and diagnostic accuracy for PCA and csPCA of MRI, PSMA-PET/CT, biopsy modalities (SB vs. MR-TB vs. PET-TB vs. PET/MR-TB), and the respective imaging classifications (PIRADS V2.1 classification, PROMISE miTNM classification V1.0, miPSMA score)
➢To determine the additive value of more than one targeted biopsy per MRI- or PSMA-PET/CT suspicious lesion
➢ To determine the concordance of tumor burden defined preoperatively by MRI and PSMA-PET/CT and tumor extent in the prostatectomy specimen using whole-mount sections
➢ To determine the frequencies of predefined adverse events CTCAE grade 3 in the context of PET/MR-TB in relation to the total number of biopsy cores taken and anticoagulants intake
➢ To determine the concordance of biomarker expression (PTEN and PSMA) between tumor-bearing prostate specimens (biopsy cores vs. prostatectomy specimens) as well as concordance between PSMA expression of PSMA-PET/CT imaging and prostatectomy specimens and tumorous lymph nodes

*PET* Positron-emission tomography, *PET-TB* ultrasound-guided PSMA-PET/CT fusion biopsy, *SOC* Standard of care, *SB* Systematic 12-core ultrasound biopsy of the prostate, *MR-TB* ultrasound-guided MRI fusion biopsy, *PET/MR-TB* combined SB + MR-TB + PET-TB, *PCA* Prostate cancer, *csPCA* clinically significant prostate cancer, defined as PCA with Gleason score ≥ 7a, *PPV* Positive predictive value, *NPV* Negative predictive value, *MRI* Multiparametric magnetic resonance imaging, *PI-RADS* Prostate Imaging-Reporting and Data System, *PSMA* Prostate-specific membrane antigen, *PROMISE* Prostate Cancer Molecular Imaging Standardized Evaluation, *miTNM* molecular imaging TNM system, *miPSMA score* molecular imaging PSMA expression score, *CTCAE* Common Terminology Criteria for Adverse Events

### Trial design {8}

The DEPROMP Trial is a prospective, interventional, exploratory investigator-initiated, single-group, cohort assessment study. After all patients have undergone PET/MR-TB, risk stratification and treatment planning are compared in a randomized, blinded fashion between the SOC (SB + MR-TB) and PET/MR-TB groups.

## Methods: participants, interventions, and outcomes

### Study setting {9}

Patients are referred to the study centers (University Hospital Bonn or the community Clinic Johanniter Hospital Bonn, Germany) because of suspected localized PCA. Suspicion of PCA is based on elevated prostate-specific Antigen (PSA) > 4 ng/ml, abnormal digital rectal examination (DRE), and/or abnormal findings on transrectal ultrasound (US).

### Eligibility criteria {10}

Patients will be screened for eligibility to participate using the inclusion and exclusion criteria listed in Table 2.

**Table 2 Tab2:** Inclusion and exclusion criteria

**Inclusion criteria**
1. Men suspected localized PCA based on at least one of the following criteria:
(a) Repeated PSA value ≥ 4 ng/ml
(b) Suspicious palpation of the prostate on digital rectal examination
(c) Tumor-suspicious findings on transrectal ultrasound
2. Age ≥ 45 and < 76 years
3. No previous prostate biopsy
4. Ability to give written informed consent, participate in and comply with study
**Exclusion criteria**
1. Allergy to the radiopharmaceutical 68 Ga-PSMA or to preparations with similar chemical structure
2. Abuse of medications, drugs, or alcohol
3. PSA level elevation > 100 ng/ml with resulting suspected advanced metastatic PCA
4. Chronic ongoing severe renal disease defined by estimated creatinine clearance < 30 ml/min

*PCA* Prostate cancer, *PSA* Prostate-specific antigen, *PSMA* Prostate-specific membrane antigen

### Who will take informed consent? {26a}

If eligible, patients will receive information sheets. Physicians of the study group will discuss the trial with patients in light of the information provided. Patients will then be able to have an informed discussion with the participating consultant. Physicians will obtain written informed consent from patients willing to participate in the trial.

### Interventions

#### Explanation for the choice of comparators {6b}

Diagnosis and risk stratification will be based on histopathological analysis and imaging information. In the control group, SOC biopsy results without PET-TB information are presented to the reviewers before they propose a treatment plan, whereas in the intervention group, all PET/MR-TB results are presented to the reviewers before they establish the treatment plan. Changes in therapeutic management include not only radical changes (localized therapy versus systemic therapy) but also variations in the local management. Therefore, study-relevant management changes are defined as any variation caused by the additive PSMA-PET/CT, including inter- and intra-modal adjustments, e.g., nerve-sparing approach or extent of lymph node dissection.

#### Intervention description {11a}

All patients will be investigated for prostate cancer by DRE, transrectal US, MRI, SB, MR-TB (standard of care), and additional PSMA-PET/CT and PET-TB.

#### Visit 1

In all patients, DRE and transrectal US will be performed. Moreover, Eastern Cooperative Oncology Group performance status, concomitant disease, and medication are assessed, and a PSA/free PSA will be determined.

#### Visit 2

##### MRI

Imaging will be conducted as the standard of care using the Prostate Imaging Reporting and Data System (PI-RADS) in all patients. Acquisition protocol includes T2-weighted sequences in transverse, coronal, and sagittal planes; diffusion-weighted imaging; and dynamic contrast-enhanced T1-weighted perfusion sequences. Two expert uro-radiologists on-site rate and report the MRI results according to PI-RADS v2.1. [21]; ≥ 3 PI-RADS-rated lesions are described including location, size, dynamic contrast enhancement, and ADC values. Furthermore, suspicious lesions are graphically annotated in the MRI sequences (Fig. 1), and suspicious lymph nodes and bone metastasis are reported. Capsular infiltration and extraprostatic extension will also be determined. The reporting uro-radiologists will be blinded to the corresponding PSMA-PET/CT report to avoid bias.

**Fig. 1 Fig1:**
[figure not shown]
Annotation of suspicious lesions on imaging. **A**–**C** Concordant positive findings of clinically significant prostate cancer (csPCA) in the peripheral zone of the right prostate lobe on multiparametric magnetic resonance imaging (MRI) and gallium-68 prostate-specific membrane antigen positron emission tomography/computed tomography (PSMA-PET/CT). In the DEPROMP Trial, uro-radiologists (**A**, **B**) and nuclear medicine physicians (**C**) annotate defined suspicious lesions in imaging layers to enable effective and clear interdisciplinary communication before targeted biopsy (TB) as demonstrated in exemplary fashion. An example of a false-negative MRI with true-positive PSMA-PET/CT in the posterior transitional zone of the left prostate lobe is shown in series **D**–**F**. The PSMA-PET/CT-guided TB detected a solitary, Gleason 3 + 4 PCA. In both cases, radical prostatectomy confirmed the risk stratification based on biopsy yields

##### PSMA-PET/CT

Imaging is performed at the Department of Nuclear Medicine of the University Hospital Bonn in all patients. [^68^ Ga]Ga-DKFZ-PSMA-11 (HBED-CC) is prepared on-site in compliance with good laboratory practice guidelines. [^68^ Ga]Ga-DKFZ-PSMA-11 will be administered based on patient weight (2 MBq/kg). After an adequate incubation time (optimal range: 50–100 min), PSMA-PET examination and non-contrast-enhanced low-dose CT are performed. Two highly experienced nuclear medicine physicians at the study site rate PSMA-PET/CTs for each patient and lesion using the PROMISE miTNM V1.0 evaluation system published by Eiber et al. [22]. According to PROMISE miTNM V1.0, intraprostatic lesions are visually graded in terms of PSMA expression by miPSMA expression scores 0 (“none,” uptake below blood pool), 1 (“low,” uptake equal to or higher than blood pool, but less than liver), 2 (“intermediate,” uptake equal to or higher than liver, but less than parotid gland), and 3 (“high,” uptake equal to or higher than parotid gland). Intraprostatic lesions with an miPSMA expression score ≥ 2 (uptake equal to or higher than the liver) are rated as positive for PCA [22]. Lesions rated with an miPSMA expression score of 1 are defined as equivocal findings. Intraprostatic extension and location of targetable lesions (miPSMA ≥ 1) are reported in detail by annotation (Fig. 1). For effective and clear interdisciplinary communication, PSMA-PET/CT findings will be additionally reported using a study-specific map derived from the PIRADS V2.1 prostate sector map [21]. In addition, the maximum standardized uptake value (SUVmax) per suspicious lesion is collected, and suspicious lymph nodes and bone metastasis as well as capsular infiltration and extraprostatic extension are determined. The reporting nuclear medicine radiologists will be blinded to the corresponding MRI report to avoid bias.

#### Visit 3

##### Prostate biopsy

The same physician performs SB and MR- and PET-targeted biopsies in one session. A pre-defined, software-assisted template is used for the institutional standardized biopsy in all participants. Due to standardization, cores 1/2/3/7/8/9 represent the outer peripheral posterolateral zone, and cores 4/5/6/10/11/12 represent the outer peripheral posteromedial zone and the central zone defined by PIRADS v2.1 sector map (Fig. 2). Biopsies will be conducted under antibiotic prophylaxis, rectal cleansing, and local anesthesia. Targeted tissue sampling will be performed from the areas classified as tumor-suspicious by MRI (PI-RADS ≥ 3) and/or PSMA-PET/CT (miPSMA ≥ 1). Up to three identified lesions on PSMA-PET/CT and/or MRI will be targeted with three biopsies per target. Software-assisted fusion technique (KOELIS Trinity®) is used for both SB and image-guided biopsies. Targeted samples are color-coded to allow for subsequent differential analysis. All biopsies are separately documented and sent for histopathological analysis.

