##### Histopathology

The analysis will be conducted according to the guidelines [4]. Specifically, specimens are labeled by location and, if applicable, whether they were obtained by SB, PET-TB, or MR-TB. Furthermore, the number of positive cores and the highest Gleason score per prostate lobe, per biopsy method, and per suspicious area (MRI and/or PSMA-PET/CT) are determined. Moreover, the loss of the tumor suppressor gene phosphatase and tensin homolog (PTEN) and PSMA expression will be determined in tumor-bearing biopsy specimens by immunohistochemistry. PSMA expression will be rated by an institutional-established valid semi-quantitative scale ranging from 0 to 3: “none,” “low,” “intermediate,” or “high,” respectively.

#### Visit 4

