#### Primary outcome

The primary outcome is the proportion of men with suspected prostate cancer (PCA) in whom the management plans are changed by additive PSMA-PET/CT-guided prostate biopsy in combination with standard of care using systematic and MRI-guided biopsy compared with SOC alone. Treatment plans are performed randomized for each patient based on information obtained by SOC biopsy or combined PET/MR-TB using questionnaires within 21 days of biopsy. The proposed treatment plans will be compared at intramodal and intermodal levels, and the number of patients with modified treatment regimens will be determined.

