#### Procedure for unblinding if needed {17b}

The urologist who performs prostate biopsy will be provided access to all available information to perform targeted biopsies and discuss the findings with patients if indicated. Moreover, a multidisciplinary tumor board will perform the final clinical assessment and make recommendations based on all information available. Herefore, biopsy and imaging results are unblinded.

However, unblinding is not foreseen at the notional management planning level by the reviewers at any time.

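### A three-target limit that reads as shared between MRI and PET can turn PET-TB from an addition into a partial substitute in men with more than three distinct lesions

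*Protocol article*

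**What the plan says.** All places are in the Protocol article.

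- **Eligible lesions (Prostate biopsy).** "Targeted tissue sampling will be performed from the areas classified as tumor-suspicious by MRI (PI-RADS ≥ 3) and/or PSMA-PET/CT (miPSMA ≥ 1". PET lesions at the lowest targetable score compete as well: "Lesions rated with an miPSMA expression score of 1 are defined as equivocal findings" (PSMA-PET/CT).
- **Limit (Prostate biopsy).** "Up to three identified lesions on PSMA-PET/CT and/or MRI will be targeted with three biopsies per target".
- **Who samples, and with what knowledge.** "The same physician performs SB and MR- and PET-targeted biopsies in one session" (Prostate biopsy). "The urologist who performs prostate biopsy will be provided access to all available information to perform targeted biopsies" (Procedure for unblinding).
- **What is compared.** The primary outcome sets PET-TB "in combination with standard of care using systematic and MRI-guided biopsy compared with SOC alone". The first secondary objective in Table 1 is "To determine the additive value of PET/MR-TB for detecting csPCA in men undergoing initial biopsy for suspected PCA compared to SOC".
- **Where the SOC result comes from.** The sections on the choice of comparators and on risk stratification (Visit 4) describe one biopsy per man. Reviewers see either all of its results or the same results with the PET-TB part held back. There is no separate SOC biopsy.
- **Labelling (Histopathology).** "specimens are labeled by location and, if applicable, whether they were obtained by SB, PET-TB, or MR-TB".

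**The concern.** An add-on comparison needs the SOC cores to be the ones that SOC alone would have produced, with the PET cores placed on top. A limit applied to the two modalities together breaks this once the lesions outnumber the places.

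Take a man with two MRI-only and two PET-only lesions. Neither scan alone exceeds three, yet one lesion must go unsampled. Two things can happen:

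- **An MRI lesion is left out.** The SOC dataset lacks cores that SOC alone would have contained, and PET-TB may be credited with a finding that MR-TB would have made.
- **A PET-only lesion is left out.** SOC is intact, but the contribution of PET-TB is understated.

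In either case the increment mixes addition with substitution. The men concerned have multifocal disease, and the Background section cites better discrimination of unifocal from multifocal disease as a benefit of PSMA-PET/CT.

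**Working it through.** **1. The plan's own figures (Sample size; 95% limits from Statistical methods).** Inputs: n = 200, p = 0.50, dropout 13%.

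- Half-width = 1.96 × √(0.50 × 0.50 / 200) = 0.0693, or 6.9 points. The stated ±6.9% is reproduced. The Wilson half-width is 6.86 points, and the Clopper-Pearson limits are 42.9% and 57.1%.
- Recruitment = 200 / (1 − 0.13) = 229.9, rounded up to 230. This is reproduced. Nothing below changes the sample size.

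**2. Can a shared limit bind when neither scan exceeds three lesions?** Let m be MRI-only lesions, p PET-only lesions and s lesions seen on both scans and counted once, with m + s ≤ 3 and p + s ≤ 3.

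| s | possible patterns | patterns with m + p + s > 3 |
|---|---|---|
| 0 | 4 × 4 = 16 | 6 |
| 1 | 3 × 3 = 9 | 3 |
| 2 | 2 × 2 = 4 | 1 |
| 3 | 1 | 0 |
| Total | 30 | 10 |

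So 10 of 30 patterns exceed three distinct lesions. This counts patterns and says nothing about how common they are. It shows only that the conflict does not need an unusually busy MRI.

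**3. Direction.** Count the csPCA add-on as men with csPCA in the full biopsy but not in SOC.

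- Leaving out an MRI target can only lower SOC detection, so it can only raise this count or leave it unchanged. It raises it only if the omitted lesion held csPCA, the other SOC cores did not find it, and PET cores found csPCA.
- Leaving out a PET-only target can only lower the count or leave it unchanged.
- For management change the direction is less certain, because plans also rest on imaging.

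**4. Bound on the primary proportion.** The share f of men with more than three distinct lesions is not in the documents, so it is assumed over a range. If every such man changed status in the same direction, the shift would be 100 × f points.

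| assumed f | men of 200 | largest shift (points) |
|---|---|---|
| 2% | 4 | 2 |
| 5% | 10 | 5 |
| 10% | 20 | 10 |
| 20% | 40 | 20 |

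The bound equals the half-width at f = 0.0693, that is 0.0693 × 200 = 13.9, or about 14 men.

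**The case against.** **The limit may be per modality.** The sentence before it uses the same *and/or* while giving each modality its own threshold. On that reading a PET lesion never takes an MRI place, and the point closes. This stands as a possible reading. The literal text still gives one number for a combined pool.

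**A condensed article need not give a ranking rule.** The adherence section mentions uniform work protocols for the biopsy procedure, and Trial status mentions a full protocol that is not shown. This stands: the absence of a ranking rule is not the point. The point is that the limit, as stated, does not fit the stated comparison.

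**An omitted MRI target often will not matter.** It is missing from both datasets, it may be benign, the 12 systematic cores may reach it, and reviewers also see imaging. Much of this stands. Systematic coverage is only partial, though: the article assigns those cores to the peripheral and central zones, while its own example of a PET-positive, MRI-negative cancer (Fig. 1) lies in the transition zone. Labelling separates cores that were taken but cannot restore a target that was never sampled.

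**Stronger readings that the documents do not support.**

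- A reader might infer that neither the SOC result nor the PET result is valid in these men. A dropped PET-only target leaves SOC intact, and a dropped MRI target leaves PET-TB's own sampling complete.
- A reader might assume a share of affected men and quote that many points as the bias. The table above is a worst case in which every man moves the same way. It also includes men whose MRI alone shows more than three lesions. If SOC has the same three-target limit, they would be limited under SOC too.
- A reader might infer that the problem is invisible in the data. MRI lesions of PI-RADS 3 or higher and PET lesions of miPSMA 1 or higher are annotated, and biopsies are documented separately by location and method. Unsampled lesions can largely be derived from these.
- A reader might conclude that MRI lesions should go first. That would decide which lesions are biopsied, and could leave PET-only lesions untested in men with three MRI targets. It is for the investigators.

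**Conclusion.** The point holds in a limited form. On its literal reading, the limit does not match the add-on comparison in the primary outcome and the csPCA objective for men with more than three distinct eligible lesions. An omitted MRI target may inflate the PET increment, and an omitted PET-only target understates PET-TB.

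The size is unknown. It depends on the reading of the limit, on a share of men that the documents do not give, and on whether the omitted lesion would have altered the plan. The worst case reaches the stated precision only at about 14 of 200 men, all moving in one direction; the actual shift may be much smaller. The sample size and its precision figure are sound. The matter is worth settling because the information needed is already being collected.

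**What to change.** **Wording.** Reconcile the limit in the Prostate biopsy section with the comparison in Table 1 and in the primary outcome by stating whether it is shared or applies per modality. Target selection and core numbers stay with the investigators. If it is per modality, nothing further is needed.

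**If it is shared:**

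1. From the existing MRI and PET annotations and the biopsy documentation, flag each man with an eligible lesion left unsampled because of the limit, by modality. Include men already biopsied.
2. Report the number of such men by modality.
3. Report the primary outcome and the csPCA add-on also without them, as a sensitivity analysis beside the main result.

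**Cost.** One clarifying sentence, a flag built from existing records, and one extra analysis. Leaving out 14 men widens the half-width to 1.96 × √(0.25 / 186) = 7.2 points. Leaving out 40 widens it to 1.96 × √(0.25 / 160) = 7.7 points. The main downside is scope: the sensitivity result applies only to men with no more than three distinct lesions, and so says less about multifocal disease.
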